### 7.2.3 Open label design

Participants will be informed of the intervention they are assigned to, since the processes for IPTp and ISTp are different, and blinding is not therefore possible. Blinding will be undertaken only for diagnostic tests performed by laboratory personnel.

### 7.2.4 Exclusion of HIV-positive women

Women who are HIV-positive or refuse an HIV test will not be included in this trial because all HIV-positive women in Malawi are eligible to receive co-trimoxazole prophylaxis of HIV-related infections, as recommended by WHO. Co-trimoxazole itself provides some protection from malaria infection, and SP is contra-indicated in women receiving co-trimoxazole. It would not be possible to include HIV-positive women in the current trial, as they cannot be included in the IPTp-SP arm. The prevalence of HIV in pregnancy women in Malawi is around 12%. It is therefore important to evaluate the potential effectiveness of ISTp in HIV-positive women, but this would require a different trial answering a different question, comparing co-trimoxazole prophylaxis alone with co-trimoxazole prophylaxis plus ISTp. At the clinics involved in this trial, HIV testing is offered routinely, and less than 1% of women refuse the test.

As this trial is designed to determine the superiority of a new, more expensive and complex intervention (ISTp) to current practice (IPTp), it is important that the current intervention is implemented in its most effective form possible. Therefore we plan to give at least three doses of SP to women in the IPTp group, consistent with current practice in Malawi. This will have the additional benefit within the trial of ensuring that participants in the IPTp and ISTp arms receive the same number of scheduled antenatal visits in the second and third trimesters of pregnancy, thus ensuring that they receive the same care in pregnancy, with the exception of the study intervention.

#### **7.2.6 Inclusion of women treated for malaria and anaemia**

Women with symptoms of malaria at enrolment will not be excluded, but will be randomized to the study groups, and treated with the case-management drug, artemether-lumefantrine (CoArtem) if they fall in the IPTp-SP group. They will not receive SP that month, because lumefantrine is anticipated to provide post-treatment prophylaxis comparable with SP (3 to 4 weeks), based on recently completed treatment studies in pregnant women in Uganda. SP will then be provided at the next scheduled visit. Women randomized to the ISTp arm will already receive DHA-PQ as the treatment drug. DHA-PQ and CoArtem have comparable efficacy in treating malaria.

Women participating in the trial will receive all usual routine antenatal care, and will also be encouraged to attend the clinic if they feel unwell between appointments. As part of this package of care, women attending with symptoms consistent with malaria or anaemia will be tested and treated as appropriate, and continue in the study. No exclusions will be made relating to testing or treatment for these conditions, as the same care will be available equally to women in both study arms, and the same care would be provided if either intervention were introduced into usual practice.

#### **7.2.7 Additional malaria testing not part of the point of care testing and treatment**

All participants who give consent will have a blood sample taken at enrolment and during the third trimester to test for peripheral malaria using standard microscopy of blood smears and PCR. The results of these tests will not become available until the end of the trial and will not be used to inform the care of the women. In this way, a point prevalence of malaria at baseline and in the third trimester can be estimated for both intervention arms, without contaminating the intervention in either arm. Testing of asymptomatic pregnant women is not usual practice in Malawi; the treatment of asymptomatic malaria in pregnancy has not yet been shown to be advantageous in women receiving IPTp; and women in the ISTp group will receive malaria testing and treatment if positive in any case; therefore no existing intervention will be withheld. This blood sample will be combined with a routine sample for haemoglobin in the third trimester, and with a second HIV screening test following the new WHO guidelines for repeat HIV testing in the third trimester.

#### **7.2.9 Stratified sampling of women with different gravidities**

We anticipate most or all of the impact on birth outcomes and morbidity to be in women in their first and second pregnancies, based on systematic review of previous trials with IPTp-SP and ITNs. However, the impact on placental malaria infection is anticipated to

occur across all pregnant women, including those in their third and subsequent pregnancies. Placental malaria and malaria at term are now recognised to be important endpoints in themselves as they have been found to be risk factors for malaria, anaemia and other infections in infants up to the age of two years, independent of the effect of malaria on gestational age low birth weight. The effect appears to be particularly evidence in multigravidae. Furthermore, IPTp is currently recommended for and provided to women of all gravidities, and it is anticipated that any alternative strategies to IPTp may also be provided to all pregnant women, if any potential benefit is identified. This trial will therefore focus on morbidity endpoints in women in their first and second pregnancies, and on malaria infection at term and delivery in women in their third to fifth pregnancies (active or past infection). They will be enrolled using a stratified sampling strategy.

#### **7.2.10 Use of a composite birth outcome as the primary trial endpoint**

In women in the first and second pregnancies, this trial aims primarily to assess the effect of the intervention on birth outcomes. A composite primary outcome of SGA, low birth weight or pre-term birth will be used because there will be more births falling into one of these categories than into a single category and malaria during pregnancy is associated with increased risk of all these three measures, including an increase in the risk of SGA in children born at term and with birth weight > 2500 g; Therefore a smaller sample size will be needed to detect a significant difference between study intervention arms than if a single outcome were used. The use of a composite outcome has the disadvantage that all events are given equal weight; however, SGA, low birth weight and pre-term births will also be reported separately as secondary analyses.

Early neonatal deaths are not included within the composite endpoint measure because the aetiological fraction of deaths due to malaria is anticipated to be small; most early postnatal deaths result from events occurring during delivery (e.g. prolonged labour).

#### **7.2.11 Assessment of adverse effects of treatment**

The safety profile of SP in pregnant women is already well documented, and this trial has very limited potential to add significantly to that body of knowledge. There has been less research into the safety of DHA-PQ in pregnancy. In this trial, too few women will receive DHA-PQ to undertake a meaningful analysis of sub-clinical effect, as DHA-PQ will only be provided to women enrolled in the ISTp arm who have a positive RDT result. However, blood samples will be taken at 14 days after treatment and the following tests undertaken to add to the body of knowledge: full blood count; blood haemoglobin levels; total bilirubin, alanine aminotransferase and creatine; and blood DHA-PQ levels. These tests will not be point of care.

Interim placental histopathology results from another trial (IPT-mon) suggest that around 28% (95% CI 19% to 42%) of pregnant women in southern Malawi may experience placental malaria infection. Around 776 participants in this trial will receive ISTp; and since only 20% to 30% of those are likely to be treated with DHA-PQ (as the rest will be RDT-negative throughout) only around 155 to 233 will receive the drug. A larger trial multi-centre study is currently ongoing to assess the safety, efficacy and tolerability of different ACT regimens for the treatment of smear-positive malaria in pregnant women in Malawi and three other African countries; 'Safe and efficacious artemisinin-based combination treatments for African

pregnant women with malaria'. This trial will include 860 women scheduled to receive DHA-PQ and laboratory testing for sub-clinical effects will be undertaken. Data from this trial will add to that knowledge base.

Although minor events will be monitored in the ISTp arm, because of difficulties in identifying appropriate comparisons, there will be no systematic comparison of minor adverse event rates between trial arms. At each study intervention visit, participants will fall into three different categories: women with or without malaria infection taking SP; RDT-positive women taking DHA-PQ; and RDT-negative women taking no drug. The three groups will be different not only in the drug taken, but in their malaria status, knowledge of their malaria status, and their knowledge of the drug taken. Unbiased comparisons between groups are therefore not possible. Follow-up for symptomatic adverse events will therefore focus on serious adverse events, adverse events serious enough to be reported to the study clinics through passive surveillance or requiring treatment, and the tolerability of DHA-PQ assessed by women's self-reports on day three after the first dose.

## 8 Study populations

### 8.1 Inclusion criteria

1. Viable singleton pregnancy
2. Gestational age 16 to 28 weeks (inclusive) by LMP (if available) or fundal height
3. No history of IPTp use during this pregnancy
4. Willing to participate and complete the study schedule
5. Has provided written informed consent
6. Resident of study area and intending to stay in the area for the duration of the follow-up
7. Willing to deliver in the labour ward of the study clinic or hospital

### 8.2 Exclusion criteria

1. HIV positive or unknown HIV status
2. Multiple gestations
3. High risk pregnancy resulting in referral to tertiary delivery facilities according to local guidelines, these include:
  - a. Age under 16 or over 40
  - b. Five or more previous pregnancies
  - c. Pre-existing illness likely to cause complication of pregnancy (hypertension, diabetes, asthma, epilepsy, renal disease, fistula repair, leg or spine deformity)
  - d. Two or more previous miscarriages or induced abortions
  - e. Previous caesarian section delivery, vacuum extraction or symphysiotomy
  - f. History of pregnancy or birth complications (pre-eclampsia or post-partum haemorrhage)
4. Severe anaemia requiring blood transfusion ( $Hb \leq 7.0$  g/dL) at enrolment
5. Known allergy or previous adverse reaction to any of the study drugs
6. Unable to give informed consent (for example due to mental disability)
7. Previous inclusion in the same study

## 9 Outcome measures

### 9.1 Primary outcome

In women in their first or second pregnancy: composite endpoint of adverse birth outcomes, defined as any of:

- Small for gestational age defined as a binary outcome of <10th percentile of fetal weight for attained gestational age using the new Landis fetal weight nomogram from the Democratic republic of Congo.
- Preterm birth (spontaneous birth before 37 weeks gestation)
- Low-birth-weight (birth weight under 2,500 grams)

In women in their third to fifth pregnancies: Malaria infection at term and delivery will be the primary endpoint, defined as evidence of current or recent infection assessed at delivery by placental histopathology ('active' or 'past' infection) or RDT (pLDH or HRP2 positive, any species) or PCR positive (any species).

### 9.2 Secondary outcomes

#### 9.2.1 Secondary efficacy outcomes

1. Placental malaria (any species):
  - a. Past infection detected by histopathology
  - b. Active infection detected by:
    - i. Histopathology
    - ii. Microscopy
    - iii. Rapid diagnostic test
    - iv. Polymerase chain reaction (PCR)
2. Maternal malaria infection (peripheral blood) at delivery, detected by:
  - a. Microscopy
  - b. RDT
  - c. PCR
3. Peripheral malaria infection during pregnancy detected by:
  - a. Microscopy
  - b. PCR
4. Birth weight
  - a. Mean birth weight (grams)
  - b. Low birth weight (<2,500 grams)
5. Gestational age
  - a. Mean gestational age at birth (grams)
  - b. Pre-term birth (<37 weeks)
6. Small for gestational age
7. Maternal haemoglobin and anaemia:
  - a. At delivery
    - i. Mean maternal haemoglobin (g/dL)
    - ii. Anaemia (Hb ≤ 11 g/dL)
    - iii. Moderate to severe anaemia (Hb ≤ 8g/dL)

- b. During third trimester
    - i. Mean maternal haemoglobin (g/dL)
    - ii. Anaemia ( $Hb \leq 11$  g/dL)
    - iii. Moderate to severe anaemia ( $Hb \leq 8$ g/dL)
- 8. Miscarriage (loss of foetus before 28 weeks gestation)
- 9. Stillbirth (birth at 28 weeks or later showing no signs of life)
- 10. Composite endpoint of the primary endpoint plus fetal loss (miscarriage or stillbirths)
- 11. Infant death
  - a. Perinatal death (stillbirth or death within 7 days of birth)
  - b. Neonatal death (death within 28 days of birth)
- 12. Malaria infection of the newborn, detected by analysis of umbilical cord blood with:
  - a. RDT
  - b. Microscopy
  - c. PCR
- 13. Foetal haemoglobin and anaemia by sampling of umbilical cord blood at birth:
  - a. Mean foetal haemoglobin (g/dL)
  - b. Foetal anaemia ( $Hb \leq 12.5$  g/dL)
  - c. Moderate to severe foetal anaemia
- 14. Incidence of documented clinical malaria episodes during the second and third trimesters of pregnancy (history of fever in last 24 hours and documented malaria microscopy or RDT positive)
- 15. Presence of any evidence of malaria infection at term (last antenatal visit), identified through microscopy or PCR, or at delivery, identified through peripheral and placental RDT, microscopy or PCR, or placental histopathology (active or past infection).
- 16. Incidence of other illness episodes apparent at scheduled antenatal clinic visits or resulting in unscheduled clinic visits
- 17. Incidence and prevalence of clinical malaria in infants by seven days and six to eight weeks determined by:
  - a. RDT
  - b. Microscopy
  - c. PCR
- 18. Prevalence of symptomatic infant anaemia at seven days and six to eight weeks
  - a. Anaemia
  - b. Moderate to severe anaemia
- 19. Incidence of other illness episodes in the infants, apparent at scheduled postnatal clinic visits or resulting in unscheduled postnatal clinic visits

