| Blood biochemistry                                    |                                   |                                        |                                                                   |                                           |                                            |                                        | *Sub-sample                               |          |                                   |                                        |
| Full blood count                                      |                                   |                                        |                                                                   |                                           |                                            |                                        | *Sub-sample                               |          |                                   |                                        |
| Blood drug levels                                     |                                   |                                        |                                                                   |                                           |                                            |                                        | *Sub-sample                               |          |                                   |                                        |
| Immunology                                            | X                                 |                                        |                                                                   | X                                         |                                            |                                        |                                           | X        |                                   |                                        |
| Peripheral malaria microscopy and PCR                 | X                                 |                                        |                                                                   | X                                         |                                            |                                        |                                           | X        |                                   |                                        |

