### 6.2 Secondary objectives

#### 6.2.1 Efficacy

To determine if ISTp-DP compared with IPTp-SP in the second and third trimesters of pregnancy is associated with:

- A decrease in the prevalence of placental malaria at delivery
- An increase in the mean duration of pregnancy or a reduction in the prevalence of pre-term birth

- An increase in mean birth weight or a reduction in the prevalence of low birth weight
- A decrease in stillbirths, neonatal deaths or perinatal death
- A decrease in pregnancy loss in the second and third trimesters
- An increase in mean haemoglobin levels or decrease in any anaemia, moderate anaemia and severe anaemia at delivery
- A decrease in the prevalence of peripheral parasitaemia at delivery
- A decrease in the incidence of clinical malaria episodes in pregnancy
- A decrease in the incidence of peripheral parasitaemia in the third trimester of pregnancy
- An increase in mean haemoglobin levels or decrease in any anaemia, moderate anaemia and severe anaemia during the third trimester of pregnancy
- A decrease in the prevalence and incidence of clinical malaria or symptomatic anaemia in infants by seven days and six to eight weeks

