#### 16.1.1 Enrolment

After informed consent has been signed, participants will be randomly allocated (see section 17.2) to receive either IPTp or ISTp (see section 15.1) and issued with a trial identity card with their unique study identification number. Participants will be informed of study intervention they have been allocated to.

At this stage study staff will ask the participant for a home or mobile telephone number if they have one, and home address or a description of the location of their home, and for their verbal consent to be visited at home two days after receiving the study drugs (if they receive DHA-PQ) and whenever they do not attend scheduled appointments.

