#### 16.1.2 Baseline assessment

A baseline assessment will be conducted for each participant comprising demographic information, socioeconomic information, insecticide treated net (ITN) and indoor residual spraying use, medical and obstetric history, and clinical assessment. Any relevant information already collected during the screening process or at previous antenatal appointments for the same pregnancy will be copied from the antenatal cards onto the CRF, so that questions, tests and examinations are not unnecessarily duplicated.

Study-relevant information recorded at the first visit will include age; area of residence; prior use of ITNs; number of previous known pregnancies and number of previous births. Clinical assessment will include height and weight, fundal height, reported date of last menstrual period and estimated gestation.

A 5 ml venous blood sample will be taken and used for both routine and study-specific testing. This will be obtained after consent for eligibility screening has been obtained but before consent for enrolment in the trial; women who have not been tested for HIV in their current pregnancy will be tested for HIV, and all women will be tested for anaemia and haemoglobin levels. Women not previously tested for syphilis in this pregnancy will be tested and treated if positive. The same blood sample will be prepared for later study-specific testing for malaria (blood smear microscopy and PCR), for markers of immunity to *P. falciparum* malaria, and for markers of iron deficiency. Aliquots of separated blood plasma will be stored at -20 or -80C for immunity studies. A filter-paper sample will be prepared and stored for future research if the woman has given her consent for this.

If not already done, an ultrasound scan will be done at this visit or at a separate visit within a month of enrolment.

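### Secondary outcome item 3 (peripheral infection during pregnancy) does not match its third-trimester objective and does not exclude the pre-randomisation booking sample or sick-visit smears

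*Combined protocol and SAP*

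**What the plan says.** Three places in the combined protocol and SAP bear on this outcome.

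- **Objective (section 6.2.1):** "A decrease in the incidence of peripheral parasitaemia in the third trimester of pregnancy".
- **Outcome (section 9.2.1, item 3):** "Peripheral malaria infection during pregnancy detected by" microscopy (3a) and PCR (3b). No trimester or visit is named.
- **Sampling rationale (section 7.2.7):** "All participants who give consent will have a blood sample taken at enrolment and during the third trimester to test for peripheral malaria". It adds that "a point prevalence of malaria at baseline and in the third trimester can be estimated for both intervention arms".

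On timing, section 16.1.2 says of the booking blood sample: "This will be obtained after consent for eligibility screening has been obtained but before consent for enrolment in the trial". Section 16.1.1 says: "After informed consent has been signed, participants will be randomly allocated". Section 16.7 adds RDT and blood smears, but not PCR, for women who come to the clinic unwell between appointments. Section 17.3.3 says only that the secondary efficacy outcomes will be analysed in a similar way to the primary one. It does not define the window for item 3.

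**The concern.** An infection found before randomisation cannot have been affected by either strategy. If a woman positive only at booking counted as an event, both arms would gain events at about the same rate, and the comparison would move towards no difference. Smears from sick visits raise a separate difficulty. They depend on who chooses to attend in an open-label trial, and they feed microscopy but not PCR, so items 3a and 3b could cover different periods.

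The measure is also unsettled. The objective asks for an incidence, but one scheduled third-trimester sample gives a point prevalence, which is the term that section 7.2.7 uses. Section 7.2.7 says the smear and PCR results become available only at the end of the trial. A window still open at that stage could be chosen with the results in view.

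**Working it through.** **1. Which samples fall within item 3.** The row "Peripheral malaria microscopy and PCR" in the section 3.2 visit table is marked at booking, the final antenatal visit and delivery. Delivery has its own outcome, item 2: "Maternal malaria infection (peripheral blood) at delivery, detected by". The scheduled samples left for item 3 are therefore booking and the final antenatal visit. The booking sample precedes trial consent (16.1.2) and randomisation follows it (16.1.1), so the booking sample is pre-randomisation. Other items in 9.2.1 do name a window: 7b (third trimester), 14 (second and third trimesters) and 15 (last antenatal visit or delivery). Item 15 pools the last antenatal visit with delivery and placental findings, so it does not isolate the third-trimester objective.

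**2. The nearest stated figure.** No rate, sample size or power is given for item 3. Section 17.1 states 81% power for a 25% reduction in placental malaria in first and second pregnancies (G1-2) at 491 per arm. The control rate of 33% is in section 4.4. With pC = 0.33, pT = 0.75 × 0.33 = 0.2475 and mean p̄ = 0.28875:

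- Power = Φ[(|pC − pT| − 1.96·SE0)/SE1]
- SE0 = √(2p̄(1 − p̄)/n) = 0.02892; SE1 = √([pC(1 − pC) + pT(1 − pT)]/n) = 0.02880
- (0.0825 − 0.05669)/0.02880 = 0.896, so power = 81.5%. The stated figure reproduces.

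For multigravidae (G3+), 20.5% v 10.25% needs 213 per arm at 80% power with a continuity correction, as stated. Without the correction, 213 per arm gives 83.7%, the starting value used below.

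**3. Effect of counting booking positives.** Let b be the booking prevalence, equal in both arms by randomisation, and p the third-trimester prevalence, independent of the booking result. Then:

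- P(any positive) = b + (1 − b)p
- The risk difference is multiplied by (1 − b)
- RR = [b + (1 − b)pT]/[b + (1 − b)pC]

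Example, G1-2 with b = 20%: control 0.20 + 0.80 × 0.33 = 0.464; ISTp 0.20 + 0.80 × 0.2475 = 0.398; RR 0.858; difference 6.6 points (0.80 × 8.25).

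The placental rates stand in for third-trimester peripheral prevalence, which the documents do not give. The values of b are assumed for the same reason.

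| Sample counted | G1-2 RR | G1-2 power (491/arm) | G3+ RR | G3+ power (213/arm) |
|---|---|---|---|---|
| Final antenatal only | 0.75 | 81.5% | 0.50 | 83.7% |
| Any, b = 10% | 0.813 | 67.9% | 0.676 | 60.9% |
| Any, b = 20% | 0.858 | 55.1% | 0.775 | 44.0% |
| Any, b = 30% | 0.891 | 44.0% | 0.838 | 32.5% |
| Any, b = 40% | 0.917 | 34.7% | 0.882 | 24.5% |

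**4. Sensitivity to independence.** Suppose booking-positive women have twice the later risk, with the overall third-trimester rate unchanged. The later risk in booking-negative women is then p/(1 + b). In G1-2 the RR becomes 0.818 to 0.935 and power is 61%, 42%, 29% and 20% across the same values of b. Both calculations assume the same relative effect in booking-positive and booking-negative women.

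**The case against.** The strongest reply is that the plan already treats booking as baseline. Section 7.2.7 names two separate point prevalences and labels the first one baseline. Section 7.1, in its overview of extra sampling, mentions only the third-trimester sample for later microscopy and PCR. Nothing combines the two samples into an ever-positive outcome. This stands. A reader might infer from item 3 that the plan counts pre-randomisation infections as events, but the documents do not say so. They fail to exclude them.

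A reader might also treat section 7.2.7 as a rival definition of the outcome. It is sampling rationale, and it covers both baseline and third trimester. The mismatch is between one objective line and one outcome line.

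On sick-visit smears, item 3 lists microscopy and PCR without RDT, which is the test set of the final antenatal sample (16.4.4), and febrile malaria episodes have their own outcome in item 14. That points away from unscheduled smears, but no sentence rules them out.

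Finally, the power figures could be read as power that the trial will lose. They cannot be, since the plan states no power for item 3. A more dramatic illustration, such as a halving of prevalence at 491 per arm, would join the G1-2 sample size to an effect resembling the G3+ assumption and would match neither stratum.

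**Conclusion.** The concern holds as a gap in definition. Item 3 lacks the window that its objective has, and its literal wording admits a pre-randomisation sample and attendance-driven smears. The word incidence in section 6.2.1 is wrong for a single scheduled sample on any reading.

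The pull towards no difference is conditional on the literal reading. Its size depends on borrowed placental rates, an assumed booking prevalence of 10% to 40%, and independence or the one alternative shown. Given those, the RR moves from 0.75 to 0.81-0.92 in G1-2 and from 0.50 to 0.68-0.88 in G3+. The direction under these assumptions is the same for any booking prevalence above zero.

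Severity is minor. This is one of 19 secondary efficacy items and does not appear among the secondary endpoints in the synopsis. Neither primary endpoint nor the sample size is affected.

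**What to change.** - Define item 3 as the prevalence of peripheral malaria infection in the scheduled final antenatal visit sample, reported by microscopy and by PCR.
- Take the visit window from the schedule once its passages are reconciled: the section 3.2 table gives 34 to 36 weeks and section 16.4 gives 34 to 37 weeks.
- State that booking samples and unscheduled-visit smears do not count towards item 3.
- In the matching objective of section 6.2.1, replace incidence with prevalence.
- Use the booking microscopy and PCR result as a baseline covariate. This is a modelling choice, not the correction of an error, but it gives a result already being collected a stated role.

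The cost is a wording change made before the end-of-trial smear and PCR results are available. No sample, visit or test is added.
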